### Enrollment and follow-up procedures

#### Screening procedures

The screening visit for ToV4 is integrated with the ART eligibility visit of the Dar es Salaam HIV care and treatment program. At the screening visit, clinic doctors identify HIV-infected adults who are eligible for ART initiation by WHO disease stage or CD4 T cell counts and refer these individuals to research nurses for ToV4 screening procedures. Research nurses assess inclusion/exclusion criteria for the trial and if eligible also seek written informed consent for a blood draw to screen serum 25(OH)D levels. In order to assess pregnancy status of potential participants, all females are asked the date of their last menstrual period and any woman who has not had their menstrual period in the previous 6 weeks is given a pregnancy test. Individuals who meet all eligibility for ToV4 screening and consent for a blood draw have 5 mL of blood collected in a red-top vacutainer tube for serum 25(OH)D assessment. At the screening visit, all participants receive treatment of comorbidities per Tanzanian standard of care and are scheduled for an ART initiation visit in 1–2 weeks in concordance with the HIV treatment program visit protocol.

#### Screening 25(OH)D assessment

Blood samples collected at the screening visit are then sent to a central laboratory where sera are separated by centrifugation. 25(OH)D concentration was then manually assessed with the commercial Immunodiagnostics (IDS) enzyme immunoassay (EIA) per kit protocols (IDS, Boldon, UK). Prior to the start of the trial we conducted a validation study of the IDS EIA using sera from our previous observational cohort of HIV-infected Tanzanian men and women initiating ART due to reports of overestimation of serum 25(OH)D by EIA [16, 43]. The validation study was conducted at the Boston Children’s Hospital Laboratory in Boston, MA, USA. In the validation study 40 randomly selected sera had 25(OH)D assessed both by the IDS EIA and by high-performance liquid chromatography tandem mass spectrometry (HPLC-MS/MS) using an API-5000 (AB Sciex, Foster City, CA, USA) as the ‘gold standard’ [44]. The IDS EIA was manually performed per commercial kit instructions. For HPLC-MS/MS testing, serum samples were first extracted and ‘cleaned up’ using the Aria-TLX-2 (Thermo Fisher Scientific, Waltham, MA, USA) after which 50 μL was mixed with acetonitrile containing internal standard of 25-hydroxyvitamin d6D3. Samples were then centrifuged and 50 μL of the supernatant was injected into the Aria-TLX-2, passed through a Cyclone-P column (Thermo Fisher Scientific), and then eluted through a Kinetex C column (Phenomenex, Torrance, CA, USA). The eluate was injected into the API-5000 for atmospheric pressure chemical ionization and passed through the triple quadrupole mass spectrometer for detection and quantified measurements. This HPLC-MS/MS method is linear up to 100 ng/mL and sensitive to 1 ng/mL. Figure 3 presents a scatterplot of the validation study results, which show the IDS EIA linearly overestimated 25(OH)D concentration as compared with the HPLC-MS/MS. Robust regression determined the line of best fit was IDS EIA 25(OH)D ng/mL = 10.451+ 0.886*HPLC-MS/MS 25(OH)D ng/mL. Accordingly, in order to enroll individuals with 25(OH)D <30 ng/mL we set the threshold for trial eligibility with the IDS EIA test kit to 25(OH)D <37 ng/mL.

**Fig. 3 Fig3:**
[figure not shown]
Scatterplot of validation study results comparing 25(OH)D concentration assessed by IDS EIA (y-axis) versus HPLC-MS/MS (x-axis). *25(OH)D* 25-hydroxyvitamin D, *EIA* enzyme immunoassay, *HPLC-MS/MS* high-performance liquid chromatography tandem mass spectrometry, *IDS* Immunodiagnostics

#### Randomization procedures

Individuals screened for 25(OH)D levels return to the clinic within 1–2 weeks for the trial randomization visit which is integrated with the ART initiation visit of the HIV treatment program. At the randomization visit, research nurses inform all screened individuals of their 25(OH)D results. Individuals with 25(OH)D levels ≥30 ng/mL are told they have adequate levels of vitamin D and are not eligible for trial enrollment. All individuals with 25(OH)D levels <30 ng/mL are informed they have low vitamin D levels as well as potential sources of vitamin D (sun exposure, oily fish, eggs, etc.). Research nurses then re-document all eligibility criteria for individuals with 25(OH)D <30 ng/mL and seek written informed consent for ToV4 enrollment.

Individuals who consent for ToV4 enrollment are individually randomized 1:1 to the vitamin D_3_ or placebo arm. Randomization procedures were designed for complete allocation concealment and blinding of all participants, clinic staff, senior research staff, and trial statisticians. Trial arm allocation is performed according to a computer-generated randomization list of 4000 individuals with sequence blocks of ten stratified by study clinic that was generated by a non-study statistician. Two non-study statisticians will hold the randomization list codes until completion of primary analyses or until requested by the Data and Safety Monitoring Board (DSMB). An independent study pharmacist prepares the vitamin D_3_ and placebo regimen by labeling bottles with participant IDs based on the randomization list. At the randomization visit, allocation concealment is performed by assigning individuals eligible for trial randomization to the next available numeric participant ID which corresponds to a set of pre-labeled regimen bottles with the same participant ID. As a result, all trial participants, research staff, and trial statisticians are not able to determine the allocated trial arm for any trial participant or identify trial participants who are on the same trial arm.

At the randomization visit, all study participants receive a full clinical examination from study physicians, and have HIV disease stage assessed according to the WHO criteria [45]. All comorbidities are treated per Tanzanian standard of care. Nurses also administer a standardized questionnaire to collect information on sociodemographics, reported symptoms during the last 30 days (fever, cough, etc), depression, anxiety, social support, and physical activity. Nurses also collect anthropometric measurements including height, weight, and mid-upper arm circumference. Participants are also asked for cell phone numbers and location of their home for follow-up visits, given the participant provides written informed consent for phone and home contact with study staff. At the end of the randomization visit, research nurses directly observe the participant taking the first supplement of the weekly regimen. The weekly regimen bottles remain in the clinic for all participants.

#### Follow-up clinic visit procedures

All participants are actively followed at weekly clinic visits for 3 weeks (week 1, 2, 3) followed by monthly clinic visits at starting at the fourth week until 12 months post ART initiation. At 12 months, participants are discharged from the trial and continue to receive standard treatment within the HIV care and treatment program but are not followed by research staff. At all clinic visits research nurses administer a questionnaire on symptoms reported within the last 30 days and collect anthropometric measurements including weight and mid-upper arm circumference. At the 6-month and 12-month visit the baseline questionnaire on sociodemographic, depression, anxiety, social support, and physical activity is re-administered. Physicians also perform a full clinical examination, assess WHO HIV disease stage, and treat all comorbidities in accordance to Tanzanian standard of care at all study visits. At week 1, week 2, and week 3 clinic visits, nurses directly observe the participant taking the trial supplement in study clinics. At the fourth week and at monthly visits thereafter until trial discharge at 12 months, participants are given regimen bottles containing 35 trial supplements to be taken daily in the home.

### Primary and secondary outcome assessment

#### Vital status assessment

Participants who do not come for their scheduled clinic appointments are contacted via cell phone and/or visited at home to assess vital status. Participants that are reached by phone or in the home are asked to come to the clinic if the participant is physically able to do so. For patients who traveled out of Dar es Salaam, we maintain contact via cell phone or with neighbors and relatives to collect information on the vital status of the participant. For participants who are confirmed to have died we administer a standardized verbal autopsy to relatives or individuals present around the time of death to assign a cause of death. Participants that die in a health facility also have events before and at the time of death transcribed from hospital records. Two seniors HIV clinicians utilize the verbal autopsy data and hospital records to establish a cause of death by consensus. A third senior clinic serves as the tie-breaker for deaths for which the first two clinicians cannot reach consensus.

#### Pulmonary TB assessment

All participants presenting with any of the following five clinical signs and symptoms at any study visit are considered pulmonary TB suspects per the Ministry of Health of Tanzania protocol: cough for 2 weeks or more, fever, 3 kg weight loss in 1 month or noticeable weight loss for new patients, night sweats, or hemoptysis. All TB suspects provide a spot sputum specimen at the clinic visit symptoms were noted and are given a sputum container for collection of early morning sputum before a second visit the next weekday. A third spot specimen is then collected under supervision by a nurse at the second clinic visit. The sputum smears are prepared and stained using Ziehl-Nielsen technique and examined for acid-fast bacilli (AFB) by trained health laboratory technologists who grade the smears on an ordinal scale following standard guidelines of the International Union Against Tuberculosis and Lung disease [46]. All TB suspects also receive a chest X-ray. During the trial the GeneXpert System (Cepheid, Sunnyvale, CA, USA) which uses the cartridge-based Xpert MTB/RIF (Xpert) assay became available for TB testing at three of the four study clinics. Participants who are sputum AFB negative for whom TB is still suspected are tested by GeneXpert for detection of Mtb. DNA. According to Tanzanian national guidelines, pulmonary TB diagnosis is made when at least one sputum smear is positive for AFB, GeneXpert detects Mtb DNA, or when there are radiological features suggestive of TB in the presence of constitutional TB symptoms. Patients start TB treatment on same the day of diagnosis.

#### Hypercalcemia assessment

All participants have serum calcium and albumin assessed at baseline, 1, 6 and 12 months. Serum calcium and albumin concentrations are assessed with the Roche Cobas Integra 400 Plus (Roche Diagnostics, Basel, Switzerland). Albumin-adjusted serum calcium concentrations are then calculated using the following equation: calcium (mg/dL) = total calcium (mg/dL) + 0.8 × [4 − albumin (g/dL)] [47]. Any participants with above the normal physiologic range of albumin-adjusted calcium (>2.6 mmol/L) are diagnosed with hypercalcemia, discontinue their trial regimen for the duration of the trial and are given appropriate clinical management. Individuals with hypercalcemia continue to be followed up until discharge of the trial and resolution of hypercalcemia. In addition participants are monitored at all clinic visits by study physicians for symptoms of hypercalcemia including: nausea, vomiting, excessive thirst, anorexia, symptoms of kidney stones, and confusion. If any of these symptoms are reported and there is no other suspected cause, study clinicians order calcium and albumin testing. At this point participants with suspected hypercalcemia stop their randomized treatment regimen until calcium testing results are returned. If albumin-adjusted calcium levels are normal for hypercalcemia suspects, the patient is allowed to re-start the regimen under discretion of study physicians. Hypercalcemia suspects with albumin-adjusted calcium >2.6 mmol/L discontinue their trial regimen for duration of the trial and are given appropriate clinical management.

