### Study population

Individuals are eligible for the trial randomization if they meet all the following inclusion criteria: (a) adult men or women aged ≥18 years old, (b) HIV-infected, (c) initiating ART at the time of randomization, (d) have low vitamin D levels with a 25(OH)D concentration <30 ng/mL at ART initiation (e) intending to stay in Dar es Salaam for at least 1 year after enrollment, and (f) provide written informed consent. Exclusion criteria include: (a) pregnancy (women of childbearing age are required to have a negative pregnancy test within a month prior to randomization) and (b) enrolled in any other clinical trial. During the trial the ART initiation criteria for the Dar es Salaam HIV treatment program changed from CD4 T cell count <350 cells/μL or WHO HIV stage 3 or 4 disease to CD4 T cell count <500 cells/μL or WHO HIV stage 3 or 4 disease in January 2016.

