### Vitamin D_3_ and placebo regimens

The investigational vitamin D_3_ trial regimen consists of oral supplements containing 50,000 IU vitamin D_3_ taken at randomization and once a week for 3 weeks at clinic visits under direct observation (four doses) followed by daily oral supplements containing 2000 IU vitamin D_3_ taken in the home starting at the fourth week until trial discharge at 1 year post ART initiation. The matching placebo regimen consists of oral placebo supplements taken at randomization and once a week for 3 weeks at clinic visits under direct observation (four doses) followed by daily oral placebo supplements taken in the home starting at the fourth week until trial discharge at 1 year post ART initiation.

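### Calcium above 2.6 mmol/L permanently stops the regimen, but no printed eligibility criterion or first-dose condition uses the baseline calcium result

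*Protocol article*

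**What the plan says.** The Study population section of the protocol article lists six inclusion criteria, all of which must be met, and two exclusions (pregnancy and enrollment in another trial). The only laboratory threshold among them is 25(OH)D below 30 ng/mL. Under Randomization procedures, nurses re-document eligibility, take consent and randomize. A physician examines every participant, and the first supplement is swallowed under observation at the end of the same visit. In the active arm that supplement is 50,000 IU, with three more at weekly intervals.

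The Hypercalcemia assessment section sets the schedule: "All participants have serum calcium and albumin assessed at baseline, 1, 6 and 12 months". Participants whose albumin-adjusted calcium is above 2.6 mmol/L "are diagnosed with hypercalcemia, discontinue their trial regimen for the duration of the trial", and they remain in follow-up. Baseline is not exempt from this rule.

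The same section adds a symptom check: "participants are monitored at all clinic visits by study physicians for symptoms of hypercalcemia". Its trigger is conditional: "If any of these symptoms are reported and there is no other suspected cause, study clinicians order calcium and albumin testing". Suspects stop the regimen until the result is back.

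**The concern.** The trial has its own calcium limit above which nobody may take the regimen, and it measures calcium in everyone at baseline. As printed, though, that measurement neither decides who is eligible nor has to be seen before the first capsule. A participant already above the limit can be given a large weekly dose that the protocol's own rule would bar. Alternatively, if the result is known, a randomization number goes to someone who cannot be treated for the whole year. The first outcome is a participant-safety matter. The second costs a little under intention-to-treat analysis.

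**Working it through.** **Tracing the printed rules for a person above 2.6 mmol/L at baseline**

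1. Eligibility (Study population): no calcium item, so the person qualifies.
2. Randomization visit (Randomization procedures): eligibility is re-documented with no calcium result named.
3. Physician examination and symptom check: the person is held only if symptoms are reported without another suspected cause. Asymptomatic elevation passes through, as do nausea, vomiting or anorexia put down to something else.
4. End of that visit: the first supplement is taken.
5. Stop rule (Hypercalcemia assessment): the regimen ends for good.

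If the result arrives after step 4, at least one dose has been taken. If it is known before step 4, the person still meets every printed criterion but may not be treated.

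**When is the baseline sample drawn?** This is not stated, and the schedule figure is not shown. Three passages suggest the randomization visit, without proving it:
- The Screening procedures section describes the screening tube for one purpose only. Those who qualify and "consent for a blood draw have 5 mL of blood collected in a red-top vacutainer tube for serum 25(OH)D assessment".
- The Laboratory investigations section places CD4 count and hemoglobin at the screening visit, but PTH and ALP at baseline.
- The Follow-up clinic visit procedures section calls the questionnaire given at randomization the baseline questionnaire.

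**Number affected.** Baseline prevalence u is not in the document.
- Per 0.1 percentage point: 4000 × 0.001 = 4 randomized; 2000 × 0.001 = 2 in the active arm.
- Illustration: active-arm number = 2000 × u × m, where m is the share missed by the symptom check. Both u and m are assumed.

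| u | m = 50% | m = 100% |
|---|---|---|
| 0.1% | 1 | 2 |
| 1% | 10 | 20 |
| 2% | 20 | 40 |

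**Exposure before the stop**, with dosing on days 0, 7, 14 and 21:
- result before the first dose: 0 IU;
- result after the first dose and by day 7: one dose, 50,000 IU;
- result on days 8 to 14: two doses, 100,000 IU.

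The only turnaround the document shows is for 25(OH)D, available at the randomization visit 1–2 weeks after screening. If calcium drawn at randomization took as long (assumed), exposure would be one to two doses.

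**Efficacy.** Inputs from the Sample size section: 4000 participants, 10% loss (1800 per arm), two-sided alpha 0.05, placebo mortality 10%, relative risk 0.70. The two-proportion power, with pooled variance under the null, is

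Φ{[d − 1.96·√(2p̄(1−p̄)/n)] / √[(p₁(1−p₁)+p₂(1−p₂))/n]}.

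- The plan's figure: p₁ = 0.10, p₂ = 0.07, d = 0.03, p̄ = 0.085. This gives 0.898, against the 90% printed in Table 2.
- With 2% of the active arm untreated: RR = 0.70 × 0.98 + 1 × 0.02 = 0.706, so p₂ = 0.0706 and power = 0.885.
- With 0.1% untreated: RR = 0.7003 and power = 0.897.

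**The case against.** The strongest case against is that this is silence in a condensed article. When the sample is drawn, how fast the result returns and whether staff look at it before dispensing are details that a full protocol would hold. The exclusion list is introduced in a way that need not be exhaustive, and the schedule figure is missing. On this view, testing everyone and stopping those above the limit is a coherent rule, and excluding them instead is a preference. No harm from one dose is shown: the section on the regimens reports weekly 50,000 IU as safe in three other patient groups. Everyone enrolled has low 25(OH)D, a physician sees each person before the first supplement, and the baseline result ends exposure once it returns. The prevalence range is assumed, and the 25(OH)D turnaround is a weak proxy because calcium runs on a different analyzer. Finally, enrollment was due to end in March 2017, so a new criterion would reach only the last recruits.

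Much of this limits the size of the point. Timing, prevalence and harm are unknown, a pre-dose check may exist elsewhere, and a change does nothing for those already randomized. It does not remove the point. Eligibility, time of first dose and the permanent stop are each stated, and following them as printed produces one of the two outcomes. The symptom hold does not cover asymptomatic elevation. The safety evidence cited is not in people with hypercalcemia, and the limit at issue is the trial's own.

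**Conclusion.** The concern holds as a modest participant-safety point that should be corrected. It rests on the trial's own 2.6 mmol/L rule, not on evidence that a single dose does harm. The number affected is unknown; the 1 to 40 in the active arm only illustrates the assumed ranges. Which of the two outcomes applies depends on when the baseline result is available, which the text does not say. If the result always precedes the first dose, nobody is harmed and the cost is a few untreated randomized participants. The efficacy consequence is negligible even at the assumed 2%. Confidence is medium, because the full protocol or the schedule figure could contain a check before dosing. If so, stating it would settle the safety part.

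**What to change.** For people who meet the 25(OH)D criterion, run the planned baseline calcium and albumin on the screening serum. The route already exists: "Blood samples collected at the screening visit are then sent to a central laboratory where sera are separated by centrifugation", and the 25(OH)D results are available by the randomization visit. Then:
- add an exclusion for albumin-adjusted calcium above 2.6 mmol/L at screening;
- require that result, alongside 25(OH)D, before randomization and the first supplement;
- refer anyone above the limit for clinical management and start ART as scheduled;
- leave the symptom hold as it is.

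This also keeps pre-existing elevation out of a safety endpoint defined as incident hypercalcemia.

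Costs:
- One exclusion line, and one line in the screening consent, which now covers a 25(OH)D draw only.
- The baseline calcium moves 1–2 weeks earlier if it is not already taken at screening. The 5 mL tube is assumed to hold enough serum.
- If 5% to 10% of those meeting the 25(OH)D criterion do not go on to randomization (assumed), the extra calcium/albumin pairs are 4000/0.95 − 4000 = 211 to 4000/0.90 − 4000 = 444. That is 1.3% to 2.8% of the 4000 × 4 = 16,000 planned.
- Eligibility narrows slightly. At the assumed 0.1% to 2% prevalence, 4000/0.999 − 4000 = 4 to 4000/0.98 − 4000 = 82 more people are needed to reach 4000.

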#### Laboratory investigations

All participants have CD4 T cell counts assessed at or before the ToV4 screening/ART eligibility visit and then every 6 months after ART initiation. Hemoglobin is also measured at the ToV4 screening/ART eligibility visit. In order to examine the effect of the vitamin D_3_ regimen on bone health, we will measure PTH and ALP at baseline, 1, 6, and 12 months for a random sample of 800 individuals (20%). We will also assess the effect of vitamin D_3_ on host immune response through measurement of IL-2, IL-12, IFN-γ, and the antimicrobial peptide cathelicidin in 800 (20%) randomly selected individuals at baseline, 1, 6, and 12 months.

#### Compliance assessment

Any trial requires a high degree of compliance with experimental regimens as non-compliance can bias results and decrease the statistical power of a study. The best way to ensure full compliance is to observe each participant ingesting treatment. In ToV4 research nurses directly monitor subjects taking the weekly trial supplements (randomization, week 1, week 2, week 3), but this type of monitoring is not practical for the subsequent daily supplements taken in the home (week 4 to month 12). In order to promote adherence during the daily regimen period, all participants are encouraged to use the daily supplements at the same time every day, to put the bottle in a visible place, and identify an adherence assistant who would remind her/him to take the supplement. Compliance with the daily ToV4 supplements will be assessed three ways: (a) direct questioning about use of the supplements in the previous 24 hours and 2 weeks, (b) pill count from returned daily regimen bottles, and (c) biochemical assessment of 25(OH)D in a subset of participants longitudinally at randomization, 1, 6, and 12 months.

